## Abstract

**Background:**

The skills of patients on oral anticoagulants are critical for achieving good outcomes with this treatment. Self-management, or the capacity of patients to control their INR level and adjust their treatment, is an effective strategy of treatment. Capacity of patients to self manage is determined by a range of factors. The identification of these factors would improve the design of self management programmes and in turn increase the number of patients able to self-manage. The objective of our study is to identify those factors that determine the ability of patients on oral anticoagulant therapy to achieve self-management of their treatment.

**Design:**

This will be a three year quasi- experimental prospective study with a control group. 333 patients on anticoagulant therapy from five health centres of the Basque Health Service are to be followed up for a period of six months each after the intervention, to assess their ability to self-test and self-manage. The intervention will consist of a patient training programme involving the provision of information and practical training concerning their condition and its treatment, as well as how to use a portable blood coagulation monitoring device and adjust their anticoagulant dose.

**Discussion:**

The ease-of-use of this technique lead us to believe that self-management is feasible and will represent an innovative advance that should have a substantial impact on the quality of life of this patients and their families as well as on the health care provision systems.

**Trial registration:**

Osakidetza Protocol Record ISCIII-11/02285, Oral anticoagulation and self-management, ClinicalTrials.gov Identifier: NCT01878539

## Background

Oral anticoagulants (OACs) are increasingly widely used for the treatment of cardiovascular diseases, such as atrial fibrillation (currently its primary indication), valvular heart disease and venous thromboembolism [1]. Indeed, it in a relatively short period of time they have become the treatment of choice for the aforementioned conditions and are currently used in 1.7-2% of the population in Spain, reaching 7-8% in people aged 65 and [2] over. OACs are effective in preventing thromboembolic events, but they have a major adverse effect, namely an increased risk of bleeding [1].

While for OACs to be safe and effective international normalized ratio (INR) values should be maintained within narrow margins, measurements outside the normal range for their condition are common in people on OAC therapy. Indeed, internal assessments in centres in our region have estimated that 35-40% of INR measurements (around 19,000) are out of the normal range. Deviation from the therapeutic range has been associated with new cardiovascular events such as the development of thrombosis or bleeding in the case of low or high INR levels respectively [3].

Numerous factors have an impact on INR levels. Keeping these levels under control and stable is difficult and requires collaboration, learning and responsibility on the part of all those involved: general practitioners and nursing staff as well as patients themselves.

The progressive increase in the number of people on OACs has led to a corresponding increase in the resources dedicated to monitoring this treatment. Indeed, some hospital haematology services have been overwhelmed by situation, and in response to this several health regions in Spain have decided to transfer the follow-up and management of these patients to primary care. In primary care centres, the role has been taken on by general practitioners and primary care nursing staff who test INR levels and adjust doses as necessary (referring patients to the Haematology unit in just 6% of cases).

In this context, an increase in the number of patients able to self-monitor would have an impact at the organisational and financial level within the health system itself [4], both for hospital haematology services and primary care, given that management has been transferred to this level of care in many cases.

Moreover, there is an international consensus that self-monitoring [2] is a key element for improving the management of patients on OAC therapy. Internationally, several pilot studies [5] have been set up exploring patient self-testing (ability to use a coagulometer for measuring INR values) and self-management (ability to adjust doses according to the INR changes). These interventions, involving active selection of patients and subsequently providing them with training, have demonstrated that around 50% of patients are able to adequately monitor and manage their treatment [6,7]. Some interventions carried out in Spain, specifically in Andalucía, Cataluña, Castilla y León and Aragón (EviBased Nurs 2005: 8: 87 doi: http://dx.doi.org/10.1136/ebn.8.3.87) [4,7] have produced results confirming these findings. Notably, in some studies it has been found that patients who self-manage have lower rates of cardiovascular events and have significantly lower rates of thromboembolic and bleeding complications [5,8].

Many patients are able to monitor and even control factors that affect the therapeutic ranges and, in such cases, it is appropriate for them to take partial responsibility for managing their treatment. For this, however, patients must be trained how to use portable coagulometers and hence monitor their INR levels themselves, supported by health professionals [8-11].

Training programmes for self-management are effective in terms of enabling patients to acquire the necessary skills, though the level of success seems to depend on various patient-related factors. Given the proven benefits of self-management, it would be useful to properly characterise these factors and use this information to successfully increase the percentage of patients on OACs able to self-manage their own treatment.

## Design

This will be a quasi-experimental prospective study with a control group. Patients on anticoagulant therapy from five health centres of the Basque Health Service are to be followed up for a period of six months after the intervention, to assess their ability to self-monitor and self-manage.

### Hypothesis

An intervention program targeting patients and caregivers based on education about their condition and training in the use of portable coagulometer to self-monitor and training on the treatment adjustment to self manage, can be effective to enable patients in OACs to self manage as well as to identify determinant factors associated with the success and failure of the program.

### Primary objectives

1. To assess the ability of patients/caregivers to self manage OAC treatment (to test INR levels with a portable coagulometer and capillary whole blood from a finger prick and to adjuste OAC doses accordingly) 2. To evaluate the impact of a range of factors on the capacity of patients on OACs to self-monitor and self-manage.

### Secondary objectives

1. To compare the incidence of adverse effects in patients in the control and intervention groups 2. To compare the rate of in-range INR (i.e., levels within the therapeutic range) in patients in the control and intervention groups 3. To assess the impact on the quality of life of the self-management programme 4.To describe the attitudes and opinions of health professionals and patients with respect to the self-management programme.

## Methods

A pilot study has been conducted, over 33 patients, to identify potential determinant factors to be studied, to assess the methodology of the intervention and any technical problems related to the use coagulometers. The pilot study has already finished and has no lead to relevant changes in the main study protocol. Their results are being processed in order to be published.

Subsequently, a multi-centre, interventional study will be performed with a control group with an overall duration of three years. The target population for this study is patients on OAC therapy for any reason, aged above 16 years and under the care of participating health centres in an urban area. These health centres cover a population of over 200,000 and currently 1.7% of this population is on anticoagulants (approximately 3400 individuals).

Patients will be excluded from the study if they do not live in the area on a regular basis, have any serious diseases (including kidney or liver failure, or any terminal conditions), have been less than six months on OAC therapy or decline to participate. From the pool of elegible patients, the sample will be randomly selected, with a number of reserve subjects. These selected patients will be provided with information about the objectives and methodology of the study and asked to participate. Among these, some will be willing to be part of the intervention group and will be included in it, and some will not be interested in receive the intervention, and these will be considered for the comparison control group, both groups of patients should provide consent for their participation in the intervention and for their clinical records to be reviewed by the research team in the case of control group. This non random patient assignation method, is the reason of this study being defined as quasi-experimental and not a clinical trial.

The proposed sample size is 333 individuals. In order to derivate predictive models based on logistic regression models it is necessary to include at least ten final events for each of the independent variable included in the model (Laupacis A et al.; Vittinghoff E et al.). It is our intent to propose a model including less than ten independent variables, so, considering “successful self management” as our final event, 100 successful subjects will be necessary to guarantee a proper convergence of the model. Published studies [7] show that the success rate in this kind of self management programs stands around 50%, so we considered that in order to compare both groups, it would be necessary to have 100 successful patient and 100 non successful. Another study of Fitzmaurice [11] shows that a 40% of participants did not complete this type of program, so 333 subjects will be necessary in order to have the required sample size.

The intervention will consist of two sessions of participative training leaded by trained nurses. First, an educational workshop will be run with the goal of improving patient understanding of their condition and OAC treatment. Then, a second workshop will be run focused on training patients how to use a coagulometer and how to adjust their OAC doses, that is, the skills necessary to self-monitor and self-manage. In this second session, a coagulometer and a record sheet will be given to each patient as well as a telephone number to seek advice for any problems or questions that may arise during the follow-up period. The follow up period will last 6 months for each subject. Several intervention groups will be constituted and the intervention will be implemented consequently for each group, giving the project a total period of three years for its execution.

During this follow up period, patient will be provided free access to sanitary advice and a monthly follow-up visit will be scheduled with their assigned health professionals. Any reported incidents and weekly INR records kept by the patients will be registered, as will be details arised during the follow up visits.

Data will be collected on the use of the coagulometer, the INR measurements, the visits and any advice or support sought during the self-monitoring period. Other potentially relevant variables will also be analysed including age; use of multiple medications; willingness to take on self-management of their condition and treatment; social and cultural status; and presence of serious illnesses, conditions associated with tremor, multiple diseases, or blindness; as well as patient knowledge of their own disease and the reason for anticoagulation treatment. Particular attention will be paid to recording any thrombotic or bleeding episodes.

The main final event, “successful self management” will be defined as patients finishing the follow up period with less than 30% of INR determinations out of range and no thrombotic or bleeding episodes.

For self-monitoring, latest generation portable coagulometers will be used; these devices have improved compared to previous models and can be linked to a computer to download the data for processing.

Patients in the control group will receive regular care from their general practitioners. Data to calculate the rate of in-range INR (levels within the therapeutic range), and the incidence of adverse effects will be retrieved from the electronic clinical record for the six months follow-up period.

The attitude of health professionals, both doctors and nurses, with regards to whether they would advise self-monitoring and management in patients on OAC therapy will be analysed, using a questionnaire prior to the start of the study.

The project has been approved by the ethical committee “Comité Ético de Investigación Clínica del Área Sanitaria de Gipuzkoa” on November, the 23th 2011.

The project is funded by Carlos III Health Institute (a grant from the Spanish Health Research Fund, FIS (PI11/02285) and “Centro de Excelencia en Investigación en Cronicidad, Kronikgune” (Kronik 11/053).

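### Controls are patients not interested in the intervention, yet no pre-study INR or event history is secured to handle that selection

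*Protocol article*

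**What the plan says.** The Methods section draws a random sample of eligible patients and then lets willingness decide the group. Those who want the training receive it; of the others, "some will not be interested in receive the intervention, and these will be considered for the comparison control group". The article is open about this: "This non random patient assignation method, is the reason of this study being defined as quasi-experimental and not a clinical trial".

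Two secondary objectives rest on the contrast between these groups: "To compare the incidence of adverse effects in patients in the control and intervention groups" and "To compare the rate of in-range INR (i.e., levels within the therapeutic range) in patients in the control and intervention groups".

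For controls, the Methods state: "Data to calculate the rate of in-range INR (levels within the therapeutic range), and the incidence of adverse effects will be retrieved", from the electronic record and for the six-month follow-up. No earlier window is named for either group. Consent to review of clinical records is mentioned for the control group; intervention patients consent to taking part in the intervention.

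Two further statements matter. Patients are excluded if they "have been less than six months on OAC therapy". The Background says of primary care that "the role has been taken on by general practitioners and primary care nursing staff who test INR levels and adjust doses as necessary".

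**The concern.** Patients who volunteer to test their own INR and adjust their own dose may well differ from those who decline in motivation, ability and adherence. Such traits can affect INR control and events without any programme. Secondary objectives 1 and 2 are the only stated comparisons of INR control and safety with usual care. A comparison of follow-up values alone cannot separate the effect of the programme from the effect of who chose it.

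Choosing a model can be left to an analysis plan. The extraction window and the scope of consent cannot, because they decide whether a baseline value will exist at all. As described, the article secures none.

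**Working it through.** **The plan's own figure.** The sample size reproduces: 10 events x 10 variables = 100 successes; 100 / 0.50 = 200 completers; 200 / (1 - 0.40) = 333.3, stated as 333. This is built for the model of self-management success. It involves no control-group size, effect size, alpha or power for intervention versus control. The 200 is 100 successful plus 100 unsuccessful completers, not 200 per group.

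**Assumed inputs (none is in the documents).** SD of the per-patient in-range share: 20 or 25 percentage points. Group sizes: 200:200 or 200:100. True programme effect: zero. Selection gap g: 5 points, the same before and during follow-up. Pre/post correlation r: 0.3, 0.5 or 0.7. All results are large-sample normal approximations.

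**Unadjusted comparison.** SE = SD x sqrt(1/n1 + 1/n2). Two-sided rejection = Phi(g/SE - 1.96) + Phi(-g/SE - 1.96).

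- SD 20, 200:200: SE = 20 x sqrt(2/200) = 2.00; g/SE = 2.50; rejection 0.705.
- SD 25, 200:100: SE = 25 x sqrt(1/200 + 1/100) = 3.06; g/SE = 1.63; rejection 0.372.

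A nominal 5% test thus rejects in 37-71% of studies. With a 3-point gap the corresponding figures are 0.323 and 0.165.

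**Regression on pre-study in-range share (ANCOVA).** For a stable gap, residual bias = g x (1 - r) and SE is multiplied by sqrt(1 - r^2).

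| r | Bias left of 5 points | Share removed | Rejection, SD 20, 200:200 | Rejection, SD 25, 200:100 |
|---|---|---|---|---|
| 0.3 | 3.5 | 30% | 45% | 22% |
| 0.5 | 2.5 | 50% | 30% | 16% |
| 0.7 | 1.5 | 70% | 18% | 11% |

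**Difference-in-differences.** SE is multiplied by sqrt(2(1 - r)), that is by 1.18, 1.00 and 0.77; at SD 20 and 200:200 it is 2.37, 2.00 and 1.55. Bias is zero if the gap is stable.

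**When the gap is not stable.** Suppose it shrinks from 5 points before the study to 2.5 during follow-up (SD 20, 200:200, r = 0.5).

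- Unadjusted: bias 2.5, ratio 2.5/2.0 = 1.25, rejection 24%.
- Difference-in-differences: bias 2.5 - 5 = -2.5, SE 2.0, so again 24% rejection, now against the programme.
- ANCOVA: bias 2.5 - 0.5 x 5 = 0.

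Each method therefore has a scenario in which it fails, which is the reason to report both. If selection acts only on the later course, the pre-study gap is zero and neither method removes any of the bias.

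**The case against.** The authors do not present the contrast as randomised; they state that assignment is not random and name the design accordingly. Objectives are normally worded as comparisons, and a condensed article commonly leaves the adjustment method to the full protocol or the analysis plan. The sentence on control data says how the follow-up outcome is obtained; it does not forbid an earlier extraction. Age, multiple medications and multiple diseases are already listed as variables to be analysed. Both contrasts are secondary. Every input to the illustration is assumed.

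Most of this stands. The absence of a named adjustment is not a finding, and a reader who infers that the plan commits to an unadjusted comparison is reading silence as a statement. What remains is the data. The only window given for controls is follow-up, record-review consent is tied to controls, and the listed covariates are not said to be collected for controls. Calling the study quasi-experimental acknowledges the selection but supplies nothing to handle it. Willingness, also on the list of variables, cannot serve as a between-group covariate because willingness to receive the intervention is what separates the groups.

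**Conclusion.** The point holds as a cheap improvement that should be made. The groups are formed by willingness, and the article as written secures no pre-study INR or event history with which to handle that selection. Under the assumptions above, a stable 5-point gap would produce 37-71% false rejection without adjustment. The true gap, SD, correlation and control-group size are unknown.

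Two stronger readings are tempting and are not supported. One is that six months of INR history exists for every patient and would remove most of the bias. The exclusion rule sets a minimum time on treatment, and testing in primary care makes earlier values likely for most participants, but nowhere is it stated that they can be retrieved. The gain from using them is also limited: at r = 0.5, ANCOVA halves a stable gap and, with SD 20 and 200:200, still leaves about 30% false rejection. Confounding through later motivation or adherence would remain untouched.

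The other is that the flaw undermines the study. The primary objectives and the 333 do not depend on the control group.

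**What to change.** - Extend record extraction to the six months before the start of follow-up, in both groups, for INR values and for thrombotic and bleeding events, where available. Report completeness by group.
- Add consent to record review for the intervention group to match that of controls.
- Collect age, multiple medications and multiple diseases for controls too, and add the indication for treatment in both groups.
- Compare the follow-up in-range share by regression on group, pre-study in-range share and these covariates, with difference-in-differences as a sensitivity analysis.
- Adjust the adverse-event comparison for the same covariates and prior events as far as event numbers allow. Pre-study INR would correct that comparison only indirectly.
- Report both results as adjusted associations and state that confounding by motivation remains.

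For controls the cost is an earlier date range in a record already being opened. For the intervention group it is a new record review and a consent line, easiest to arrange before enrolment.

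### The two groups' adverse events come from different sources, so the planned safety comparison could partly measure how events are found

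*Protocol article*

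**What the plan says.** The first item under Secondary objectives in the protocol article is "To compare the incidence of adverse effects in patients in the control and intervention groups".

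The Methods then describe how events become known in each group.

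- **Intervention group.** During the six months, "a monthly follow-up visit will be scheduled with their assigned health professionals". The data kept are described as follows: "Any reported incidents and weekly INR records kept by the patients will be registered, as will be details arised during the follow up visits". Patients also receive a telephone number that they can call for advice. The paragraph on data from the self-monitoring period adds: "Particular attention will be paid to recording any thrombotic or bleeding episodes".
- **Control group.** "Patients in the control group will receive regular care from their general practitioners". In the next sentence, data for the in-range INR rate and "the incidence of adverse effects will be retrieved from the electronic clinical record for the six months follow-up period". The consent sentence earlier in the Methods mentions agreement "for their clinical records to be reviewed by the research team in the case of control group".

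The article describes no common event source, common event definition or blinded assessment for the two groups.

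**The concern.** A comparison of incidence needs the same chance of finding an event in each group. Here one group has extra scheduled contacts and study registration of incidents, while the other relies on what routine care happened to write down. A thrombosis or major bleed that leads to hospital care would probably reach the record in either group. A nosebleed or bruising might be mentioned at a study visit and never be entered for a control.

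The likely direction is more events found in the intervention group. That matters because the Background cites lower thromboembolic and bleeding complication rates as a reason to favour self-management. Unequal detection could mask such a benefit or suggest a harm that is not there. Later analysis cannot repair this, because an event that was never recorded cannot be recovered by modelling. The problem is also separate from selection by willingness, which the article acknowledges: adjusting for patient characteristics does not correct for how events were found.

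**Working it through.** **1. Sources side by side**

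| Feature | Intervention | Control |
|---|---|---|
| Setting | Self-management with monthly study visits | Usual general-practice care |
| Event source described | Reported incidents, visit details, patient records | Electronic clinical record |
| Window | Six months | Six months |
| Role in secondary objective 1 | One side of the comparison | Other side of the comparison |

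The window has the same length. The source does not match.

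**2. The plan's only sample-size figure**

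The Methods give 333 subjects: 100 successes / 0.50 = 200 completers, and 200 / (1 − 0.40) = 333.3. This reproduces, but it sizes the prediction model. It says nothing about adverse-event rates or their detection, so it cannot be used to size the bias.

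**3. Illustration of the bias (all capture rates are assumptions)**

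Observed ratio = true ratio × (capture in intervention / capture in control).

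With a true ratio of 1.00 and 90% capture in the intervention group:

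- control capture 75%: 0.90 / 0.75 = 1.2
- control capture 60%: 0.90 / 0.60 = 1.5
- control capture 50%: 0.90 / 0.50 = 1.8
- control capture 85%, a closer case: 0.90 / 0.85 = 1.06
- equal capture: 1.00

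If self-management truly cut events by 30% (assumed true ratio 0.70), the first three cases would show 0.70 × 1.2 = 0.84, 0.70 × 1.5 = 1.05 and 0.70 × 1.8 = 1.26. The benefit is shrunk, then lost, then reversed.

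**4. Chance of a false signal (a second set of assumptions)**

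Take 200 patients per group, a true six-month risk of 10% in both, 95% capture in the intervention group and a two-sided 5% test of two proportions. The observed risk is 0.10 × capture, so 9.5% in the intervention group.

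| Control capture | Observed control risk | Observed ratio | Chance of a significant excess in the intervention group |
|---|---|---|---|
| 90% | 9% | 1.06 | about 4% |
| 80% | 8% | 1.19 | about 8% |
| 70% | 7% | 1.36 | about 15% |
| 50% | 5% | 1.90 | about 41% |

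With equal capture, the chance in this one direction would be 2.5%. The risk of a false finding is thus modest when the gap is small and serious only when it is large. The distortion of the estimate is present throughout.

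**The case against.** **The retrieval sentence might cover both groups.** Taken alone, it could. But it follows directly on the sentence about control-group care, and the consent sentence mentions record review for controls. The control reading is the natural one. If both groups were meant, one clarifying sentence would settle it.

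**Controls are not unobserved.** This stands. The Background says that general practitioners and primary care nurses test INR and adjust doses in this setting, so controls have recurring contacts at which bleeding can be noted. The gap may be smaller than the lower assumed capture rates imply, and its size is unknown.

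**Events are not actively sought by telephone.** This also stands. A reader might infer active telephone follow-up, but the number is for patients to call, and no structured event question at visits is described. The study-driven difference is the scheduled visits and the registration of incidents.

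**Drop-out might be thought to leave intervention patients with no event source.** The documents do not say so. The 40% is non-completion in a cited study, used to inflate the sample size, and nothing says that leavers lose safety follow-up. The consent clause is awkwardly worded and does not exclude access to intervention patients' records.

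**Drop-out might be thought to push the ratio towards 0.8.** If 40% left on average halfway (assumed), the remaining person-time would be 1 − 0.40 × 0.5 = 0.80. In a person-time rate both events and denominator shrink: 0.80 / 0.80 = 1.00 when leaving is unrelated to events. The 0.8 would need events divided by all enrolled patients without censoring, which the article does not plan.

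**A common record may not equalise detection.** This is fair, since extra visits can themselves create entries in the record. It shapes the remedy below.

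**Conclusion.** The point holds as one of unequal ascertainment in a secondary comparison, concerning mainly minor events. Followed as written, the article sets visit-registered and patient-reported events in one group against record-retrieved events in the other. The expected direction is an apparent excess in the intervention group, or a hidden benefit.

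The size cannot be derived from the documents. The spurious ratio of 1.2-1.8 rests entirely on assumed capture of 90% against 50-75%, and it falls towards 1.0 as control capture approaches that of the intervention group. The conclusion also rests on reading the retrieval sentence as applying to controls. The comparison could mislead; the text does not show that it must. The primary objectives are not affected by this point. It should be fixed because the remedy is cheap and the analysis cannot supply it later.

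**What to change.** For secondary objective 1:

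- Take thrombotic and bleeding events in both groups from the electronic clinical record, with one event definition and one extraction form, over the same six-month window.
- Include every intervention patient, whether or not they complete the programme.
- Confirm that the intervention consent covers record review, and extend it if it does not.
- Make events leading to hospital or emergency care the main comparison, because study visits may themselves generate record entries for minor events.
- Report visit- and patient-reported events in the intervention group descriptively, outside the between-group comparison.

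The cost is record extraction for the intervention group and a consent check. If the consent has to change, the ethics committee that has already approved the project may need to see it. The downside is that minor events are no longer formally compared between groups, which narrows the objective.
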